### Secondary outcome measure

The study will have one secondary outcome: 1) Assessment of the strength of the pelvic floor muscles (PFM) by PERFECT scheme.

The PFM assessment will be held before treatment (baseline- 0 week), and after the last treatment session (10 weeks). The first step bladder emptying will be requested to participant. After, the participant will be instructed to lay-down in supine position, with the lower limbs flexed, and the feet on the stretcher [15]. Prior to the PFM assessment explanation about the sequence of the PERFECT scheme will be done. Three domains of PERFECT will be used: Power, Endurance and Fast. Power (P) will be measured by Modified Oxford scale [23], which is a subjective measurement of the maximum voluntary contraction (MVC) from 0–5. We will considered the PFM strength as: 0 = no contraction- absence of muscle contraction, 1 = flicker contraction- outline of tremulous contraction (not sustained), 2 = weak contraction (which is sustained with little intensity), 3 = moderate contraction (slight lift of the examiners fingers without cranial movement), 4 = good contraction (elevation of the vaginal wall with compression of the examiner’s fingers towards to the pubic bone) and 5 = strong contraction (stronger compression of the examiner’s fingers towards the pubic bone combined with cranial movement) [24]. After strength classification, Endurance (E), referring to muscle resistance, will be assessed identifying duration of contraction up to 10 seconds using a chronometer. Fast (F) consists to the ability to perform up to 10 flicks contractions, the participant will be asked to perform a sequence of 10 MVC and the number of effective contractions will be recorded [25].

### Statistical analysis

The study will be run as a superiority trial. The statistical analysis will follow the per-treatment concept. Statistical analysis will be performed using SPSS software version 24.0 for Windows (IBM Corp., Armonk, N.Y., USA). The variables will be described by the mean and 95% confidence interval (95% CI). The distribution of normality will be analysed by the Shapiro-Wilk test. To analyse the effect of group and currents, ANOVA for repeated measures will be performed. The Mauchly’s test will be performed to test the hypothesis of sphericity and when if this violated the hypotheses, the analyses will be based on the Greenhouse-Geisser test. Peer-to-peer comparisons will be performed using the Bonferroni Post-Hoc test. The significant level adopted will be 5% (p ≤ 0.05).

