### Clinical assessment

#### Physiotherapeutic evaluation

Potential participants who fulfil the eligibility criteria undergo baseline assessments. The protocol will include anamnesis and physical assessment, the clinical screening will be carried out at São Paulo State University and will take approximately 30 minutes.

A registered physiotherapist with 8 years of experience on urogynecological examination, and who has a Master in Gynecology and Obstetrics field supervised by physiotherapist that has more than 30 years of urogynecological assessment experience will perform the evaluation. Both assessors will not be enrolled on the screening, randomization and/or treatment routine to ensure blinding assessment regardless the treatment type.

The first step of data collection will be related to anthropometric data (age, weight, height, and BMI), personal information, demographic partner (profession, race and education) and pathological and clinical history. The personal data of the participants will be numerically coded and stored in a database.

The second step of data collected will be the physical examination. PFM function will be assessed through the PERFECT scheme [15] and will be held in a reserved and adequate room. In addition, they will answer four different questionnaires regarding UUI. The International Consultation on Incontinence Questionnaire- short form (ICIQ-SF) [16], the Overactive Bladder Questionnaire (OAB-V8) [17], the International Consultation on Incontinence Questionnaire Overactive Bladder (ICIQ-OAB) [18] and the Incontinence Severity Index (ISI) [19]. At the end of the baseline assessment and before the first treatment session, participants will receive the voiding diary and instructions to complete it at home during 3 different days. All questionnaires, including the voiding diary, will be administered in Portuguese (Brazil) according to their respective validated versions.

The same blinded assessor will evaluate the participants before treatment (baseline- 0 week), during the treatment (5 weeks) and after the last treatment session (10 weeks).

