### Sample size and power analysis

A priori sample size calculation was performed using the G* Power 3.1 software. As the innovative comparisons methodology of this trial did not allow us to state our sample calculation on literature data, we calculated our sample size, based on F tests, ANOVA: repeated measures, within-between interactions, an effect size f of 0.17 were calculated considering a direct method using a small partial eta square (*n*^2^) of 0.03. Considering that we selected 5 therapies with potential treatment effects and we expect minimal differences between them, we considered the small effect size calculated by this appropriated method. In addition, we selected a power of 0.85, α error probability of 0.05, number of groups 5, number of measures 3, correlation among repeated measures of 0.5 and nonsphericity correction of 1 and a 10% dropout rate which estimated the recruitment of 105 participants, 21 per group.

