### Outcome measures

#### Primary outcome measure

The primary outcomes will be: 1) UI severity and 2) quality of life.

1) ISI is a validated questionnaire to Portuguese, that classify UI according to severity by multiplying two simple and brief questions about incontinence frequency and volume. The severity score is stratified into mild (one to two points), moderate (three to six points), severe (eight to nine), or very severe (total of 12 points) [19]. The ISI questionnaire will be applied in all time-points.1) Voiding diary is a self-real-life-assessment of voiding habits [22]. The 24-hour voiding diary shows greater acceptance by patients, but three-day voiding diary seems to be more suitable for possible evaluative interpretations [3]. The participants will fulfill during entire 3-days (72h) detailed information (including time of the event) about fluid intake (quantity), voiding (volume for each), leakage (time and associated reasons) and pad changes [22]. The voiding diary will be applied in all time-points.2) The ICIQ-SF is a brief self-administered questionnaire combined severity and bother-score through 4 questions about incontinence frequency, volume, impact of UI in daily life and self-diagnosis questions about mechanism reasons. The higher the score obtained is, the worse the quality of life related to that domain is [16]. The ICIQ-SF questionnaire will be applied in all time-points.2) The OAB-V8 will be used to assess the impact of overactivity bladder symptoms on quality of life. It is a questionnaire composed of 8 questions about the discomfort caused by the symptoms. The responses range from 0 to 5 points and in the sum of the results, if the total is ≥ 8, it will be considered as a probable diagnosis for UUI [17]. The OAB-V8 questionnaire will be applied in all time-points.2) The ICIQ-OAB questionnaire provides an assessment measure for voiding frequency, urgency, nocturia, and UI. It is composed of six specific questions about voiding symptoms correlating with quality of life, and the higher the score the worst the impairment [18]. The ICIQ-OAB questionnaire will be applied in all time-points.

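### The repeated-measures ANOVA needs all three visits, so one missed visit discards a woman's other values for that instrument and exposes the week-5 comparison to bias if loss differs between arms

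*Protocol article*

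**What the plan says.** The Statistical analysis section fixes the method: "To analyse the effect of group and currents, ANOVA for repeated measures will be performed". It adds that "The Mauchly’s test will be performed to test the hypothesis of sphericity", with Greenhouse-Geisser as the fallback and Bonferroni pairwise tests, and that "Statistical analysis will be performed using SPSS software version 24.0 for Windows". The Methods part of the Abstract repeats the same sequence. On the analysis set, the section says only: "The statistical analysis will follow the per-treatment concept". The term is not defined.

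Assessments are planned at weeks 0, 5 and 10 (Physiotherapeutic evaluation). Under Primary outcome measure, each of the five instruments (ISI, voiding diary, ICIQ-SF, OAB-V8, ICIQ-OAB) is collected every time; for example, "The ISI questionnaire will be applied in all time-points". Pelvic floor strength, the secondary outcome, is measured only at weeks 0 and 10.

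The Sample size and power analysis section assumes "number of measures 3, correlation among repeated measures of 0.5 and nonsphericity correction of 1 and a 10% dropout rate". Dropout is handled there by recruiting more women. The article mentions no imputation, no mixed model and no rule for an incomplete series.

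**The concern.** The sphericity test identifies the procedure as the classical one with one row per woman, not a likelihood mixed model. That procedure needs every visit value of an outcome. If one is missing, the woman leaves the analysis of that instrument at all time points, including those where she was measured. Two things follow.

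- **Collected data are set aside.** A woman measured at weeks 0 and 5 but not at week 10 contributes nothing. Because deletion is per instrument, the five primary instruments may be analysed on different sets of women.
- **The week-5 comparison is conditioned on the future.** It includes only women who were also seen at week 10. If the women lost are those doing poorly at week 5, and more are lost in one arm, that arm's week-5 mean looks better than it is.

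The second matters here because the sample-size section expects only small differences between the arms, and the Background and Discussion describe the currents as differing in comfort. Unequal loss is therefore plausible, though the article does not predict it.

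**Working it through.** **1. The plan's own figure.** Inputs from Sample size and power analysis: partial eta squared 0.03, alpha 0.05, power 0.85, k = 5 groups, m = 3 measures, correlation 0.5, nonsphericity correction 1, dropout 10%.

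- f = √(0.03/0.97) = 0.1759 (printed as 0.17).
- For the within-between interaction, λ = f²·N·m/(1 − ρ), df1 = (k − 1)(m − 1) = 8, df2 = (N − k)(m − 1).
- With N = 95: λ = 0.03093 × 95 × 3/0.5 = 17.6, df2 = 180, power 0.853.
- Adding 10%: 95 × 1.1 = 104.5, rounded up to 105; or 95/0.9 = 105.6, rounded up to 106. The stated 105 reproduces.

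The plan thus already budgets for about 95 complete rows. Ten women may be lost (105 − 95) before planned power suffers.

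**2. Missed visits.** The article gives no rate, so these rates are assumptions. If each follow-up visit is missed independently with probability q, the expected number of complete rows is 105(1 − q)², and 105(1 − q) women have a week-5 value.

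| q | Complete rows | Women with week 5 | Power, f = 0.1759 | Power, f = 0.17 |
|---|---|---|---|---|
| 5% | 95 | 100 | 0.853 | 0.823 |
| 10% | 85 | 94 | 0.800 | 0.767 |

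The first row equals the planned loss. Only loss beyond it erodes planned power.

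**3. Week-5 bias when loss follows response.** Setting for a simulation of 400,000 women per arm: no true difference, three visits with correlation 0.5, and withdrawal after week 5 depending on the week-5 score through a logistic curve with slope 1 to 2 per SD. The withdrawal rates and slopes are assumptions. The table gives the between-arm difference in week-5 means, in favour of the arm with more withdrawal.

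| Dropout in the two arms | Women with all visits | All observed week-5 values |
|---|---|---|
| 10% and 10% | about 0 SD | about 0 SD |
| 5% and 15% | 0.08–0.13 SD | about 0 SD |
| 5% and 25% | 0.17–0.24 SD | about 0 SD |

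When withdrawal was unrelated to the score (slope 0), the difference was also about 0 at every pair of rates.

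**4. Which contrasts move.** Let selection on the week-5 score shift an arm's week-5 mean by δ. With equal correlations of 0.5, its baseline and week-10 means each shift by 0.5δ.

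- Change from baseline to week 5: δ − 0.5δ = 0.5δ. The between-arm bias in this change is half the figures above: 0.04–0.07 SD at 5% versus 15%, and 0.09–0.12 SD at 5% versus 25%.
- Change from baseline to week 10: 0.5δ − 0.5δ = 0.

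If the correlation falls with the time between visits, the last cancellation is no longer exact.

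**The case against.** **The article never says complete cases.** It condenses a fuller protocol, and missing-data handling is often left to an analysis plan. Imputation followed by this ANOVA would contradict nothing printed. This stands as a limit: the exclusion follows from the named method on unimputed data and is not a stated rule. The method itself is fixed, however, and nothing shown offsets its consequence.

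**The analysis set may already exclude these women.** If per-treatment means women who completed treatment, one who withdraws after week 5 is out before any model is fitted, and a mixed model on that set would omit her too. This stands. A reader might infer that the ANOVA alone causes the loss and that changing the model alone cures it; the documents do not support that. On a completers-only set, the model matters only for treated women who miss an assessment or a diary, and no bias was computed for them.

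**The bias can be made to look larger.** Removing exactly the worst 20% at week 5 from one arm shifts its mean by φ(z)/(1 − d) = 0.280/0.8 = 0.35 SD. A reader might take that as the bias, but it assumes a hard cut-off and no loss elsewhere. If 10% are lost overall and one arm loses 20%, the other four average (50 − 20)/4 = 7.5%. The same cut-off shifts those by about 0.15 SD, leaving about 0.20 SD between arms.

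**The link from comfort to withdrawal is thin.** The article describes differences in comfort but ties none of them to withdrawal. Intensity is to stay below pain, and women who cannot commit to the full course are ineligible. This stands: unequal, response-related loss is an assumption.

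**Conclusion.** The point holds in limited form. As written, the primary analysis sets aside collected values from any woman with an incomplete series on an instrument, and its week-5 comparison depends on who was also seen at week 10.

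The size depends on the loss. With 10% spread equally over the arms there is little bias, and planned power is intact at about 95 complete rows. With unequal loss that follows the week-5 score, the week-5 means are distorted by roughly a tenth of an SD at 5% versus 15% and up to about a quarter at 5% versus 25%.

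Two stronger readings are not supported. The trial is not underpowered because of this, since the inflation covers the expected loss. Nor is the end-of-treatment change biased under the plan's own assumption of one common correlation. The conclusion assumes no imputation before the ANOVA. The three-visit argument applies to the primary instruments only.

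**What to change.** In the Methods part of the Abstract and in Statistical analysis, make the primary analysis a likelihood-based mixed model for repeated measures (SPSS MIXED), with group, visit and group-by-visit as fixed effects and an unstructured covariance over visits. Fit it to every observed visit of every randomised woman. The Mauchly and Greenhouse-Geisser steps then belong only to the ANOVA on complete series, which is kept as a sensitivity analysis.

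State openly that this replaces the per-treatment set for the primary analysis. Without that change, the new model would not recover women who withdraw if per-treatment means treatment completers.

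The cost is the change of analysis set, reliance on data being missing at random given the observed visits, and slightly more analysis work. The software and the collected data stay the same, and no extra women or visits are needed.

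### The analysis sentence names one factor twice and omits the group-by-time interaction that sized the trial, and the baseline score is not used as a covariate

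*Protocol article*

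**What the plan says.** All of these places are in the protocol article.

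- **Statistical analysis:** "To analyse the effect of group and currents, ANOVA for repeated measures will be performed". Mauchly's test, a Greenhouse-Geisser fallback and Bonferroni pairwise comparisons follow. No time factor, interaction or baseline covariate is named. The abstract also plans a repeated-measures ANOVA without saying which effect is tested.
- **Sample size and power analysis:** the calculation is "based on F tests, ANOVA: repeated measures, within-between interactions", with "number of groups 5, number of measures 3, correlation among repeated measures of 0.5" and "nonsphericity correction of 1 and a 10% dropout rate". The effect size is f = 0.17, derived from a partial eta squared of 0.03. The target is power 0.85 at alpha 0.05, "which estimated the recruitment of 105 participants, 21 per group".
- **Randomization, allocation and blinding** and **Currents:** five arms, each receiving one current.
- **Physiotherapeutic evaluation** and **Primary outcome measure:** assessments at weeks 0, 5 and 10, with every primary instrument applied at all three. Under **Secondary outcome measure**, pelvic floor strength is measured at weeks 0 and 10 only.

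**The concern.** The sentence that should say which effect answers the trial's question does not do so. Group and currents are one factor, and the effect used to size the trial is missing. Even if currents is a slip for time, the sentence lists two main effects and still not the interaction.

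The choice matters because the candidate effects behave differently. Randomisation makes the expected arm difference at week 0 zero. A group main effect over weeks 0, 5 and 10 averages that zero into the treatment comparison. Bonferroni comparisons of marginal group means do the same, and the text does not say whether the pairwise comparisons use those means or the week-10 means. The interaction is not diluted in this way. With the tested effect left open, it could also be settled after the data are seen.

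A second, smaller point holds under either reading. The baseline score is collected on every primary instrument but is not named as a covariate, although it could sharpen the week-10 comparison at no cost.

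**Working it through.** **Inputs from the Sample size section:** k = 5 groups, m = 3 measures, ρ = 0.5, nonsphericity correction 1, alpha 0.05, dropout 10%. The printed f is 0.17; unrounded, f = √(0.03/0.97) = 0.1759.

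**1. The plan's own figure.** For the interaction, λ = f²·N·m/(1−ρ), with (k−1)(m−1) = 8 and (N−k)(m−1) degrees of freedom.
- At f = 0.1759, N = 95 is the smallest total reaching 0.85: λ = 0.03093 × 95 × 3/0.5 = 17.63, power 0.853. Then 95 × 1.1 = 104.5, so 105. (Dividing by 0.9 gives 106.)
- At f = 0.17 and N = 95: λ = 0.0289 × 95 × 3/0.5 = 16.47, power 0.823.

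So 105 reproduces, and it is a number for the interaction test.

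**2. The group main effect at the same f.** λ = f²·N·m/(1+(m−1)ρ), with 4 and 90 degrees of freedom at N = 95.
- f = 0.17: λ = 0.0289 × 95 × 3/2 = 4.12, power 0.31.
- f = 0.1759: λ = 4.41, power 0.33.

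Reaching 0.85 would take about 315 and 295 analysable women respectively.

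**3. The same true effect for both tests.** Equal f does not mean equal truth for two different effects, so a fixed truth is also needed. Assume evenly spaced arm effects, no difference at week 0, and a size that gives the interaction f = 0.17 (power 0.823 at N = 95).

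| Assumed time course | Share of week-10 difference left in the three-visit mean | Main-effect power |
|---|---|---|
| Linear growth | (0 + ½ + 1)/3 = 1/2 | 0.46 |
| Full effect by week 5 | (0 + 1 + 1)/3 = 2/3 | 0.59 |
| Effect only at week 10 | (0 + 0 + 1)/3 = 1/3 | 0.17 |

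**4. A scenario matching the trial's hypothesis.** Assume both medium-frequency arms are better by 0.6 SD at week 10, the other three arms are equal, and there are 95/5 = 19 women per arm. The mean arm effect is 1.2/5 = 0.24. The sum of squared deviations is 2 × 0.36² + 3 × 0.24² = 0.432, and 19 × 0.432 = 8.208. The variance of a three-visit mean is (1 + 2 × 0.5)/3 = 2/3.
- Linear growth: λ = 8.208 × (1/2)²/(2/3) = 3.08, main-effect power 0.24.
- Full effect by week 5: λ = 8.208 × (2/3)²/(2/3) = 5.47, power 0.41.
- Effect only at week 10: λ = 8.208 × (1/3)²/(2/3) = 1.37, power 0.12.

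**5. Value of the baseline covariate, like for like.** Per-woman variance in SD² units is 2(1−ρ) = 1.00 for change from baseline and 1−ρ² = 0.75 for the baseline-adjusted score, a 25% reduction. In the step 4 scenario, λ = 8.208/1.00 = 8.21 for change and 8.208/0.75 = 10.94 after adjustment.

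| Week-10 test | Change from baseline | Baseline-adjusted |
|---|---|---|
| 4-df comparison of five arms | 0.59 | 0.73 |
| 1-df contrast, two medium-frequency arms against the other three | 0.81 | 0.91 |

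**The case against.** A reader might infer that the trial will test the group main effect and so will not run the test it was powered for. The documents do not establish this. Mauchly's test and the Greenhouse-Geisser correction, planned in the same section, concern only within-subject terms (time and group-by-time); a between-group main effect needs neither. With the sample size section and the three assessment times, this points to a group-by-time ANOVA and a slip in the wording. That part of the objection stands, so every dilution figure is conditional on the other reading.

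A reader might also set the main effect's 0.24 (linear growth), or the interaction's 0.47 in the same scenario, against 0.91 for the adjusted contrast. That mixes 4-df and 8-df omnibus tests with a 1-df pooled contrast. Much of the gap comes from degrees of freedom and pooling arms, not from the handling of baseline. The fair gain from adjustment is the one in step 5: 10 to 14 percentage points.

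It can further be said that a group-by-time ANOVA with baseline as a level is a valid randomised comparison, and that an article may leave covariates to a fuller plan. Both are fair, so baseline adjustment is a recommended improvement, not the correction of an invalid method. Neither answer removes the mismatch: the article does state its test, and the effect stated is not the one in its sample size section.

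**Conclusion.** The point holds as a mismatch that must be reconciled. The analysis sentence names one factor twice and omits both time and the interaction on which the 105 rests. The sample size itself reproduces and is not at fault.

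The consequence depends on what is run. If it is the interaction, power is 0.82 to 0.85 with 95 analysable women, as planned. If it is the group main effect, power is about 0.31 to 0.33 at the plan's f, or 0.12 to 0.41 under an assumed 0.6 SD benefit in both medium-frequency arms, depending on the time course. The bite on pairwise comparisons of visit-averaged means is similar in kind: one half, two thirds or one third of the week-10 difference remains.

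Under either reading, adjusting for baseline would cut variance by 25% relative to change from baseline. The figures use the plan's correlation of 0.5. The 0.6 SD benefit, the spacing of arm effects and the time courses are assumptions, since the article gives none. That week 0 is a repeated level is inferred from the three measures; it is unavoidable for pelvic floor strength if that outcome is analysed by repeated-measures ANOVA.

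**What to change.** Replace the sentence with a named primary comparison for each primary outcome: the baseline-adjusted difference between arms at week 10. It can come from an ANCOVA at week 10, or from a mixed model on weeks 5 and 10 with arm, visit, arm-by-visit and the baseline score. Make the Bonferroni comparisons on the week-10 adjusted means.

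At minimum, name the group-by-time interaction as the tested effect, so that it agrees with the Sample size section, and state that pairwise comparisons are made at week 10 and not on means averaged over visits.

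The cost is a little more analysis work. No new data or participants are needed.

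### Plain Bonferroni for the pairwise arm comparisons is valid but somewhat conservative; Tukey between arms, with Holm elsewhere, would recover a few points of power within the same 5% familywise error

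*Protocol article*

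**What the plan says.** The Protocol article plans a repeated-measures ANOVA at the 5% level, with Greenhouse-Geisser if sphericity fails, and then: "Peer-to-peer comparisons will be performed using the Bonferroni Post-Hoc test". The abstract says the same. The Statistical analysis section also describes variables by mean and 95% confidence interval. It does not say whether the pairs are arms, visits, or both.

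The Sample size and power analysis section sizes the trial on a different test, "based on F tests, ANOVA: repeated measures, within-between interactions", with "number of groups 5, number of measures 3, correlation among repeated measures of 0.5 and nonsphericity correction of 1". It ends with "a 10% dropout rate which estimated the recruitment of 105 participants, 21 per group". On the size of the contrasts it says: "Considering that we selected 5 therapies with potential treatment effects and we expect minimal differences between them".

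**The concern.** No separate contrast between medium and low frequency currents is planned, so the pairwise step is the only planned analysis that can say which current does better than which. The authors expect those differences to be small, and the arms are small too.

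Bonferroni treats the pairwise tests as if nothing were known about how they relate. The ten arm pairs share arms, so their test statistics are correlated, and Bonferroni does not use that. Part of the 5% allowance goes unspent, and some true differences are missed that another standard procedure would detect with the same error control.

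**Working it through.** **The plan's own figure.** Inputs from Sample size and power analysis: partial eta squared 0.03, power 0.85, alpha 0.05, k = 5 groups, m = 3 measures, correlation 0.5, nonsphericity correction 1.

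- f = √(0.03/0.97) = 0.1759 (printed as 0.17).
- λ = f²·N·m/(1 − ρ) = 0.03093 × 95 × 3/0.5 = 17.6; df1 = 4 × 2 = 8; df2 = 90 × 2 = 180.
- Power at N = 95 is 0.853. Then 95 × 1.10 = 104.5, rounded to 105. The stated total reproduces from the unrounded f.
- Analysable per arm: 95/5 = 19.

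**Pairwise step.** Assumptions, none stated in the article: arms compared at one visit, two-sided tests, normal outcomes with equal variances, differences d in SD units.

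- Pairs: 5 × 4/2 = 10. Bonferroni level per pair: 0.05/10 = 0.005. Residual df: 95 − 5 = 90.
- Critical |t|: Bonferroni 2.878. Tukey, the 5% studentized-range point for 5 means divided by √2, is 2.784. Ratio 2.878/2.784 = 1.034.
- Smallest observed difference declared significant, critical t × √(2/19) with √(2/19) = 0.3244: Bonferroni 0.93 SD, Tukey 0.90 SD.
- True familywise error of Bonferroni when no arm differs: the probability that the studentized range exceeds 2.878 × √2, which is 0.039. In 200,000 simulated trials it was 3.9%, against 5.0% for Tukey.

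**Power per true pair.** Bonferroni and Tukey are from the noncentral t with noncentrality d·√(19/2). Holm is from the simulation with two arms better than the other three.

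| d | Unadjusted | Bonferroni | Holm | Tukey |
|---|---|---|---|---|
| 0.5 | 33.2% | 9.7% | 10.3% | 11.3% |
| 0.8 | 68.4% | 34.6% | 37.8% | 38.1% |
| 1.0 | 86.2% | 58.2% | 63.0% | 61.8% |

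Over Bonferroni, Tukey gains 1.6, 3.5 and 3.6 points; Holm gains 0.6, 3.2 and 4.8.

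**Chance of at least one true pair** (simulation):

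| Pattern | Bonferroni | Holm | Tukey |
|---|---|---|---|
| Two better arms, 0.5 SD | 33.6% | 33.6% | 37.8% |
| Two better arms, 0.8 SD | 76.3% | 76.3% | 79.8% |
| One better arm, 0.8 SD | 64.0% | 64.0% | 67.9% |

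Holm's first step is the Bonferroni threshold, so it cannot improve on the first rejection.

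**What drives the low power.** At d = 0.5 even an unadjusted test has only 33% power. With 21 analysable women per arm instead of 19, Bonferroni power at d = 0.8 is 39.5% instead of 34.6%, a larger change than the move to Tukey.

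**The case against.** The strongest reply is that nothing here is wrong. Bonferroni holds the familywise error at or below 5%, needs no equal-variance or sphericity structure, covers arm and visit comparisons under one rule, and has simple matching simultaneous intervals. The article leaves the family undefined, as a condensed report may, so the count of ten is an inference. The calculations use normal data, whereas the Incontinence Severity Index takes only a few ordered values.

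All of this stands, and it limits the point to efficiency. It does not remove it. For balanced between-arm comparisons Tukey uses the equal-variance model that the ANOVA already assumes, rejects every pair that Bonferroni rejects, and keeps matching intervals. Holm needs no assumption beyond Bonferroni's.

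A reader might infer that true differences are being missed for no return. That goes too far: the properties listed above are a real return, and the loss is a few points.

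A reader might also want the sharpest available rule, Shaffer's step-down after a significant omnibus test. With two better arms at 0.8 SD it reaches about 41% per pair and 82% for at least one pair. But its divisors presuppose an omnibus arm test at the visit analysed, which the plan does not contain. Its first threshold (|t| = 2.70) lies below Tukey's (2.78), so a pair could be declared significant while its Tukey interval includes zero. That happened in about 19% of simulated trials at 0.8 SD and 22% at 1 SD. Nor is it always stronger: with one better arm at 0.8 SD it finds at least one pair in 66% of trials, against 68% for Tukey.

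**Conclusion.** The plan fixes a valid method where a slightly more powerful one is available at almost no cost. The advantage is about 2 to 4 points per pair for Tukey, with about 4 points on the chance of detecting at least one pair at 0.5 or 0.8 SD, and about 1 to 5 points per pair for Holm, with none on the chance of detecting at least one pair. These figures rest on ten arm pairs at one visit, 19 women per arm, equal variances, two-sided tests and differences of 0.5 to 1.0 SD; the article gives no pairwise difference to use instead.

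This is a minor improvement. It should not be read as an error or contradiction in the protocol, or as the main reason the pairwise comparisons are weak. That reason is the arm size, which was set for an omnibus interaction test.

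**What to change.** In the Statistical analysis section and the abstract, replace the Bonferroni sentence with wording such as: *At a given visit, the five arms will be compared in all ten pairs by Tukey's procedure (Tukey-Kramer where arm sizes differ), with simultaneous 95% confidence intervals. Where the equal-variance structure does not apply, including comparisons between visits, Holm-adjusted p-values will be reported.*

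This also states the family for the arm comparisons. If the team intends a wider family, such as arms by visits, it should say so, and the figures above would change.

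The cost is one change of wording, with no extra participants or data. Tukey relies on the equal-variance model already behind the ANOVA, and Holm has no simple matching intervals.
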